### Outcome measures

#### Primary outcome measure

The primary outcome measure is the reduction of depressive symptoms measured with the 28-item version of Inventory of Depressive Symptoms (IDS). The IDS is a measure of symptom severity in depression that has been used to assess acute and longer-term outcomes and has highly acceptable psychometric properties (Cronbach's alpha = .92) [21,22]. The IDS self-report version will be administered at baseline, after 8, 16 and 32 weeks and at the end of the study, at 52 weeks follow-up. Patients with a 50% symptom reduction on the IDS, are responders [13]. Remission is defined as an IDS score of 13 or less.

#### Secondary measures of outcome/predictors of response

To assess chronic depression and co morbid disorders at baseline and at the end of the study patients will receive a diagnostic interview using the M.I.N.I. plus [19,20].

Information on demographic factors (age, gender, marital status, education, professional occupation) will be collected in the baseline interview and at the end of the study.

Putative modifiers of effect are well known risk-factors for chronic depression [24], these are: level of functioning, which will be measured using the WHODAS [25], social contacts and social participation using the Loneliness & Affiliation Scale [26] and the Social Participation Scale [27], locus of control using the Mastery Scale [28] and psychological well being using the Psychological Well Being Scales (PWB) [29]. Physical health and diseases will be measured by a validated Dutch questionnaire [30], psychological mindedness using the Lack of Psychological Mindedness (LPM) [31] and parental relationship using the Remembered Parenting Scale (RRP) [31]. The Mood Disorder Questionnaire (MDQ) [32] will be used to measure bipolar symptoms, number of depressive episodes in the past five years using the Life Chart [33], anxiety using the Beck Anxiety Inventory (BAI) [34], alcohol dependence using the Alcohol Use Disorders Identification Test (AUDIT) [35], recent trauma using the Brugha questionnaire [36] and childhood trauma using the Nemesis questionnaire [37]. Personality will be measured using the NEO-Five Factor Inventory (NEO-FFI) [38] and working alliance using the Working Alliance questionnaire [39].

All measures of outcomes are widely used internationally, are reliable and valid, also for usage in the Netherlands.

#### Interventions

For this project 'the founder' of CBASP, [name], came to Amsterdam to train the 25 therapists participating in this study. A four day workshop was given during which the basic techniques of CBASP were taught. Five therapists, subsequently, followed an intensive training by [name] in the US to become CBASP Supervisors. They will supervise the participating therapists during the study. The therapy will be carried out as specified in the CBASP protocol [40-42]. The treatment protocol for the therapists and manual for the patients have been translated into Dutch. All therapists have to treat two patients under supervision before being allowed to treat patients in the study. All CBASP sessions will be audio taped, and the supervisors will review the audiotapes to assess the psychotherapists' adherence to the treatment procedures ([name] (1995). Adherence Scale. Unpublished Scale. Richmond, VN: Virginia Commonwealth University). Supervision will be given on a weekly basis.

##### CBASP

The central idea of CBASP is that chronically depressed patients fail to recognize the connection between their behavior and interpersonal/environmental consequences. In other words, they do not grasp their own contribution to the life difficulties they encounter. The major goals of CBASP are to help patients 1) to understand the consequences of their behavior, 2) to change their patterns of coping, and 3) to improve their interpersonal skills [9].

CBASP is highly structured, focuses on teaching social problem skills, and makes use of regular homework assignments. The main focus is on interpersonal problems with significant others, but also in the therapist-patient relationship. The relationship with the therapist is used as a tool to help patients to become more aware of their impact on others and to distinguish between adaptive and maladaptive relationships [9].

CBASP consists of a total of 26–30 sessions in a period of a year. CBASP starts with bi-weekly sessions in the first 4 weeks followed, in principle, by one session per week from week 5–16. If establishing the therapeutic relationship proves particularly difficult, the two-weekly sessions can be prolonged for four more weeks. After 16 weeks (16–20 sessions), 4 sessions will be given once every two weeks during weeks 17–25, and as a maintenance treatment there will be 6 monthly sessions of CBASP during weeks 26–52.

##### Treatment as usual

At the three sites, treatment as usual is based on the existing Dutch multidisciplinary guidelines for depression [18]. This means that, besides optimal medical care, treatment as usual can consists of evidence-based psychotherapies, such as Cognitive Behavioral Therapy, Interpersonal Psychotherapy, or Short Psychoanalytic Supportive Psychotherapy [43]. Other interventions that may be part of the treatment offered for chronically depressed patients are supportive or structured activities and treatments that focus on relaxation, assertiveness, running, or other tasks. The treatment package received by patients in the treatment-as-usual condition will be registered throughout the study.

##### Pharmacotherapy

In both conditions drug treatment will be given, consisting of guideline' driven antidepressant medication [18]. The pharmacotherapy will be supported by 'clinical management' [44]: brief sessions in which patients will be informed about the importance of adherence and the effects and side effects of medication. The psychiatrist will change the dose or medication when necessary. The use of medication (name, dose given, and blood levels if available) will be registered for all patients participating in the study. Patients who refuse to use medication will not be excluded, because CBASP has also been found to be effective as a monotherapy for chronically depressed patients [13].

#### Economic evaluation

An economic evaluation will be performed from a societal public health perspective. All direct and indirect costs will be taken into account. Both direct costs within the health care system (e.g., costs of visits to GP, specialist, and therapist, hospital admissions, and medication use) and direct costs outside the health care system (e.g., costs of self medication, consultations with complementary medicine, and informal care) will be measured and valued. All direct costs will be considered because it is difficult to discern which costs are associated with the depressive disorder and which not. The cost-price of the CBASP intervention will be assessed using the bottom-up method. Data on health care utilization and work absenteeism are collected by the Perceived Need for Care questionnaire (PNCQ) [45] and the Trimbos/iMTA questionnaire for Costs associated with Psychiatric Illness (TIC-P) [46], which patients will fill out four times during the study, at baseline, after 16 weeks, after 32 weeks and at the end of the study, after 52 weeks. Medicine utilization will be registered at baseline and during the study until the end. Costs of health care utilization will be calculated using cost prices, if available. Otherwise tariffs will be used. Indirect costs will be calculated using the friction cost method.

#### Sample size

Based on the findings of the study of Keller and colleagues [13] it is estimated that the addition of CBASP to the existing treatment will lead to 25% more response in the intervention condition compared to the control condition. To demonstrate this difference 60 patients in each condition (beta 0.80 and alpha 0.05) are necessary [47]. Assuming a drop-out percentage of 25%, this means that 160 participants need to be recruited.

#### Analysis

Analysis of covariance, controlling for baseline value will be used to estimate the overall treatment effectiveness (difference in IDS score) at follow-up. The primary analysis will be by 'intention to treat' using double sided tests. Further exploratory analyses will also assess the impact of other explanatory factors and will model the time course of effects using the 16-week and 32-week measurements in a panel analysis. Sensitivity analyses will include estimating 'on treatment' effects, CACE (complier average causal effects), and imputation of any missing values. More sophisticated techniques will be used, like GEE analysis, to measure the longitudinal effects.

The main aim of the economic analysis is to compare the two groups in terms of mean costs and cost-effectiveness. Analysis will be performed according to intention-to-treat principle. The primary outcome measure of the study will be included in the cost-effectiveness ratios. Cost-effectiveness ratios and cost-utility ratios will be calculated using bootstrapping techniques according to the bias corrected percentile method. Bootstrapped cost-effect pairs will be graphically represented on a cost-effectiveness plane. Sensitivity analyses will be performed to study variations in prices or resource uses that are uncertain and significantly contribute to the total costs.

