**Methods/Design:**

The purpose of the present paper is to report the study protocol of a multisite randomized controlled trial testing the effectiveness of 'Cognitive Behavioral Analysis System of Psychotherapy' (CBASP) for chronic depression in the Netherlands. In this study, CBASP in combination with medication, will be tested versus usual secondary care in combination with medication. The aim is to recruit 160 patients from three mental health care organizations. Depressive symptoms will be assessed at baseline, after 8 weeks, 16 weeks, 32 weeks and 52 weeks, using the 28-item Inventory for Depressive Symptomatology (IDS). Effect modification by co morbid anxiety, alcohol consumption, general and social functioning and working alliance will be tested. GEE analyses of covariance, controlling for baseline value and center will be used to estimate the overall treatment effectiveness (difference in IDS score) at post-treatment and follow up. The primary analysis will be by 'intention to treat' using double sided tests. An economic analysis will compare the two groups in terms of mean costs and cost-effectiveness from a societal perspective.

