#### Assessments

Data are collected at five points in time: at baseline (T0), after 8 weeks of treatment (T1), after 16 weeks of treatment (T2), after 32 weeks of treatment (T3), and at the endpoint, after 52 weeks of treatment (T4). The Quick Inventory of Depressive Symptomatology self-report [23] will be assessed monthly. Table 1 summarizes the measures that are used at each point. The assessments will be performed by an experienced research nursing staff. At baseline and endpoint there will be a face-to-face interview besides the written questionnaires; the three assessments in between consist of written questionnaires only. The research nursing staff from the three participating organizations will participate in a two-day training course to make sure the measures are conducted the same way at the different locations.

**Table 1 T1:** Summary of measures

**Measure**	**Baseline**	**8 week follow-up**	**16 week follow-up**	**32 week follow-up**	**52 week follow-up**

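### The exploratory time-course model names only the 16- and 32-week measurements; naming all four post-baseline IDS visits would be a free improvement

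*Protocol article*

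**What the plan says.** The visit schedule is consistent throughout the protocol article. The Abstract states: "Depressive symptoms will be assessed at baseline, after 8 weeks, 16 weeks, 32 weeks and 52 weeks". The section on the primary outcome measure repeats it: "The IDS self-report version will be administered at baseline, after 8, 16 and 32 weeks and at the end of the study, at 52 weeks". Table 1 marks the IDS at all five time points, and the Assessments section lists week 8 as T1.

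The Analysis section makes three statements that bear on this point:
- The main estimate is a baseline-adjusted analysis of covariance of the IDS at follow-up, by intention to treat.
- Further exploratory analyses "will model the time course of effects using the 16-week and 32-week measurements in a panel analysis".
- GEE will be used for longitudinal effects, with no visits listed.

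The Abstract gives GEE a more central role, adjusted for baseline and center, but ties it to effects at post-treatment and follow-up. It does not mention week 8 in that connection.

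**The concern.** The visits for the time-course model are spelled out, so this is a stated choice and not a detail left open. The choice omits the first post-baseline IDS without giving a reason.

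A time-course analysis is meant to show when and how the arms separate. By the protocol's own session schedule, most of the CBASP course has been given by week 16, the first visit in the panel. The first score in the model then comes at the end of the most intensive phase, and nothing in the model describes what happened within it. A patient with a week-8 score who leaves before week 16 also adds no post-baseline IDS to the panel.

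**Working it through.** **1. Visits collected and visits named**

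| Post-baseline IDS | Collected (Abstract, Assessments, Table 1, Primary outcome measure) | Named in the panel model (Analysis) | Named elsewhere in an analysis |
|---|---|---|---|
| Week 8 | yes | no | no; GEE lists no visits |
| Week 16 | yes | yes | – |
| Week 32 | yes | yes | – |
| Week 52 | yes | no | presumably the follow-up of the analysis of covariance |

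Read literally, the panel uses two of the four post-baseline visits. Week 52 presumably has its place in the main analysis. Week 8 has none that is stated.

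**2. Share of CBASP given by week 16**

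Inputs from the CBASP section: 16–20 sessions by week 16, 4 sessions in weeks 17–25, 6 monthly sessions in weeks 26–52, and a stated total of 26–30.
- The stated total reproduces: 16 + 4 + 6 = 26 and 20 + 4 + 6 = 30.
- Share by week 16: 16/26 = 62% and 20/30 = 67%.
- Share of calendar time: 16/52 = 31%.

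So roughly two thirds of the sessions fall in just under a third of the year, and week 8 is the only post-baseline IDS inside that period.

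I give no session count up to week 8, because it depends on how the early schedule is read. The section says "CBASP starts with bi-weekly sessions in the first 4 weeks followed, in principle, by one session per week from week 5–16" and also that "the two-weekly sessions can be prolonged for four more weeks". Taken as twice a week, the first passage gives 4 × 2 + 12 = 20 sessions by week 16. With the prolongation it gives 8 × 2 + 8 = 24, which lies outside the stated 16–20. Those passages need to be reconciled in their own right. The 62–67% rests only on the stated totals.

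**3. Patients who leave between weeks 8 and 16**

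The Sample size section assumes 25% drop-out among 160 recruited, that is 0.25 × 160 = 40 patients. Its timing is not given, so the number leaving in this window could be anything from 0 to 40. For each of them the panel as worded has no post-baseline IDS, whereas a model with week 8 has one.

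**4. Precision (illustration on assumed values)**

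The document gives no between-visit correlation. Assume one correlation ρ between all visits, baseline included, and complete data. The variance of a baseline-adjusted, time-averaged effect over m post-baseline visits is then proportional to f(m) = [1 + (m − 1)ρ]/m − ρ².

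| ρ | f(2) | f(3) | f(4) | SE ratio, 3 vs 2 visits | SE ratio, 4 vs 3 visits |
|---|---|---|---|---|---|
| 0.3 | 0.560 | 0.443 | 0.385 | 0.890 | 0.932 |
| 0.5 | 0.500 | 0.417 | 0.375 | 0.913 | 0.949 |
| 0.7 | 0.360 | 0.310 | 0.285 | 0.928 | 0.959 |

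Each ratio is the square root of the two f values divided. Adding week 8 cuts the standard error by about 7–11% if the panel has two visits, and by about 4–7% if week 52 is already in it. The time-averaged effect also changes meaning when a visit is added, so this is only a guide to scale.

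**The case against.** The strongest reply is that the panel analysis is exploratory. The research questions concern effectiveness, cost-effectiveness and predictors of response, and speed of onset is not among them. The article condenses a fuller protocol, and an analysis plan may settle the visits. The GEE analysis is not restricted to any subset of visits, so week 8 may already enter there. All of this stands and limits the weight of the point. It does not remove it, because the one sentence that lists visits leaves week 8 out and no other sentence assigns it.

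A reader might infer more than the document supports:
- *That the 8-week IDS is thrown away.* Its use is unspecified, not excluded, because of the GEE statement.
- *That the effect is most informative before week 16.* Session density alone does not show this. Usual care may include active psychotherapy, and no session schedule is given for it.
- *That week 8 has the least attrition.* This is plausible, but only an overall drop-out of 25% is given.
- *That the early phase goes wholly unmeasured.* The 16-week IDS records the state at its end, and "The Quick Inventory of Depressive Symptomatology self-report [23] will be assessed monthly". That no analysis is described for the monthly series is a detail an article may leave to the full plan, and is not a defect.

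**Conclusion.** The point holds as a free improvement. As worded, the time-course model leaves out the only post-baseline IDS taken within weeks 1–16, the phase that holds 62–67% of the CBASP sessions, and gives no reason. What is lost is mainly the shape of the effect in that phase, together with the post-baseline scores of an unknown number of patients who leave between weeks 8 and 16. The 4–11% gain in precision is secondary and depends wholly on the assumed correlations of 0.3–0.7.

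The primary intention-to-treat comparison does not depend on the panel sentence. The sample size of 60 per arm and 160 in total rests on response rates, and it does not change either.

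**What to change.** In the Analysis section, name the 8-, 16-, 32- and 52-week measurements in place of the 16- and 32-week ones. Fit them in one longitudinal model, for example the GEE already planned, adjusted for baseline IDS and, as in the Abstract, for center, with arm-by-visit terms so that the difference can be read at each visit. If week 8 is left out on purpose, state the reason.

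One caution applies to GEE. Without weighting or imputation it does not in general protect against drop-out that depends on earlier scores. If week 8 is also meant to help with later missing values, use it in the imputation already listed among the sensitivity analyses, or fit a likelihood-based repeated-measures model.

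The cost is wording only. There are no new assessments, no added burden on patients and no change in sample size. Naming the visits in advance also removes any later choice, made with the data in view, about whether week 8 counts.

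### The primary ANCOVA is labelled intention-to-treat, but the Analysis section imputes only as a sensitivity analysis, the Abstract names GEE instead, and neither reliably handles symptom-related drop-out

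*Protocol article*

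**What the plan says.** The Analysis section gives the main estimator: "Analysis of covariance, controlling for baseline value will be used to estimate the overall treatment effectiveness (difference in IDS score) at follow-up". It adds: "The primary analysis will be by 'intention to treat' using double sided tests". Missing data are mentioned once, among secondary work: "Sensitivity analyses will include estimating 'on treatment' effects, CACE (complier average causal effects), and imputation of any missing values". The interim visits are exploratory; the plan "will model the time course of effects using the 16-week and 32-week measurements in a panel analysis". GEE comes last, as an extra: "More sophisticated techniques will be used, like GEE analysis, to measure the longitudinal effects".

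The Abstract differs. There, "GEE analyses of covariance, controlling for baseline value and center will be used to estimate the overall treatment effectiveness", at post-treatment and follow-up, again under intention-to-treat. Centre is a covariate in the Abstract but not in the Analysis section.

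The Sample size section requires 60 patients per condition and continues: "Assuming a drop-out percentage of 25%, this means that 160 participants need to be recruited". The Assessments section and Table 1 schedule the IDS at baseline and at weeks 8, 16, 32 and 52, and call week 52 the endpoint.

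**The concern.** An ANCOVA on one follow-up score can use only patients who have that score, unless missing values are filled in. The Analysis section keeps imputation for sensitivity work, so the headline estimate would rest on observed outcomes. The article is not silent here: it gives imputation a role, and that role is not in the primary analysis. An analysis plan that followed it faithfully would produce an observed-case result under an intention-to-treat label.

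At stake is the answer to the first research question. The interim IDS scores are the data that could correct for drop-out related to the observed course of symptoms. They are collected, but the ANCOVA does not use them. If the relation between course and drop-out differs by arm, the estimate shifts, possibly in favour of CBASP, and a later sensitivity analysis does not change the headline figure.

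The Abstract's GEE would use the interim scores, but the two sections then disagree on the primary estimator. Ordinary unweighted GEE also has its own condition: missingness must be completely random or depend only on covariates in the model.

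**Working it through.** **1. The plan's own numbers.** Response rates of 48% and 73% come from the Background (the cited US trial). The difference of 25 points, alpha 0.05 and power 0.80 (printed as beta 0.80) come from the Sample size section. I take alpha as two-sided and 48% as the control rate. With mean rate 0.605:

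n per arm = [1.96·√(2·0.605·0.395) + 0.8416·√(0.48·0.52 + 0.73·0.27)]² / 0.25² = [1.355 + 0.5625]² / 0.0625 = 58.8, so 59, against 60 stated.

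Inflation: 120 / (1 − 0.25) = 160, exactly as stated. The plan therefore treats drop-out as loss from the analysed number: 160 − 120 = 40 patients, or 20 per arm.

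**2. When observed-case ANCOVA is biased.** Let e be a patient's residual given arm and baseline IDS. The bias is approximately E(e | observed, CBASP) − E(e | observed, control). It is zero if missingness depends only on arm and baseline, and it cancels if selection on later symptoms is the same in both arms. It does not cancel if selection differs.

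**3. Size.** Simulation with 400,000 patients per scenario. All of the following are assumptions, not protocol figures: IDS SD 12; correlation with week 52 of 0.4 for baseline and 0.7 for week 32; 25% of week-52 scores missing per arm; interim scores complete; logit P(missing) = a + b × (week-32 IDS / SD), with b = 1, 0 or −1. Entries are IDS points in favour of CBASP.

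| Missingness mechanism | True 0: observed-case | True 5: full data | True 5: observed-case | True 5: imputed from interim IDS |
|---|---|---|---|---|
| Completely random | 0.05 | 5.02 | 5.00 | 4.99 |
| Baseline only | 0.02 | 5.04 | 5.05 | 5.06 |
| Week 32, same in both arms | −0.04 | 5.02 | 5.07 | 5.06 |
| Worse scores leave, CBASP arm only | 1.37 | 4.98 | 6.32 | 4.98 |
| Opposite directions in the arms | 2.72 | 5.04 | 7.75 | 5.03 |

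Bias with a true effect of 5: 6.32 − 4.98 = 1.34 and 7.75 − 5.04 = 2.71. With no true effect, spurious benefits of about 1.4 and 2.7 appear.

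**4. Does the Abstract's GEE solve it?** Two further set-ups used SD 12, correlation 0.75 (between adjacent visits in set-up A) and a true difference of 5. A had 21–25% drop-out, with log-odds 1 per SD of change at the previous visit; B had about 23–29%.

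| Set-up, mechanism | Observed-case ANCOVA | Exchangeable GEE | Alternative |
|---|---|---|---|
| A, CBASP arm only | 6.3 | 5.2 | unstructured GEE 5.1 |
| A, opposite | 7.6 | 5.5 | unstructured GEE 5.2 |
| B, CBASP arm only | 6.4 | 5.6 | imputation from interim IDS 4.9 |
| B, opposite | 7.9 | 6.5 | imputation from interim IDS 5.0 |

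Share of bias removed by exchangeable GEE:
- A: (1.3 − 0.2)/1.3 = 85% and (2.6 − 0.5)/2.6 = 81%.
- B: (1.4 − 0.6)/1.4 = 57% and (2.9 − 1.5)/2.9 = 48%.

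An independence working correlation gave the same result as observed-case ANCOVA in A. GEE therefore helps, but by an amount that depends on a working correlation the article does not name and on the mechanism.

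**5. A likelihood-based mixed model.** With 80 per arm, SD 12, adjacent-visit correlation 0.75, a true difference of 5 and 21–25% drop-out, the means over 800 simulated trials were:
- CBASP arm only: observed-case ANCOVA 6.0, mixed model 5.1.
- Opposite mechanisms: 7.0 and 5.0.
- Same mechanism in both arms: 4.8 and 4.9.

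Under completely random drop-out the ANCOVA variance was still about 11% larger.

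**The case against.** The strongest reply is that the primary model is not settled as an ANCOVA on completers. The Abstract names GEE, which uses the interim scores of patients who later leave. This stands: the observed-case description fits the Analysis section only, and the firm defect is that the two sections disagree.

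Second, drop-out from treatment is not the same as a missing IDS. The outcome is self-reported, and on-treatment and CACE analyses presuppose that some patients who leave treatment still give outcomes. The 25% is an allowance in a responder calculation, not a rule to exclude 40 people. This also stands, so 40 is an upper figure under that allowance.

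Third, a reader might infer that drop-out in this unblinded trial will have different causes in the two arms, making bias likely. The documents do not support that. Usual care may itself include cognitive behavioural, interpersonal or supportive psychotherapy, and antidepressant treatment is planned in both arms. No section shows that reasons for leaving differ. In set-up A, halving the strength of the one-sided mechanism brought the ANCOVA estimate down to about 5.5.

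Fourth, it would be too strong to say that GEE is valid only under completely random drop-out; dependence on model covariates (arm, baseline, centre) is also allowed.

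Finally, missing-data detail is often left to the analysis plan. That is true of covariance structures and delta values. It does not cover the placing of imputation outside the primary analysis, which the article itself fixes.

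The exploratory panel analysis also leaves out week 8, but that does not touch the headline result.

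**Conclusion.** The concern holds in a limited form. As the Analysis section is written, the intention-to-treat label and the specified method do not agree: patients without a final IDS drop out of the primary estimate and their interim scores go unused. The Abstract specifies a different estimator.

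The estimate can be biased; the documents do not show that it will be. The size is about 1 to 3 IDS points where strong mechanisms differ between arms, and near zero where missingness depends only on arm and baseline or works alike in both. These figures rest on the assumed SD of 12, correlations of 0.7 to 0.75 and the assumed drop-out models, none of which the article gives. Choosing the Abstract's GEE would reduce the exposure but not reliably end it.

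Severity: should-fix. A reader might go further and call the whole trial analysis a completers' analysis, or not intention-to-treat at all. The Abstract's GEE, and the sense of intention-to-treat as analysis in the arm assigned, do not allow that.

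**What to change.** Name one primary analysis, in the same words in the Abstract and the Analysis section, that includes all randomised patients and is valid under missing-at-random. Either of these would do:

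- a likelihood-based mixed model on the IDS at weeks 8, 16, 32 and 52, with baseline IDS, centre, visit and treatment-by-visit; or
- multiple imputation of missing IDS scores, done separately by arm from baseline and the interim scores, followed by the ANCOVA with baseline and centre.

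State the time point of the primary contrast. The Assessments section calls week 52 the endpoint, while the Abstract speaks of an overall effect at post-treatment and follow-up. Keep the observed-case ANCOVA as a sensitivity analysis, and add one for data missing not at random, for example a delta-adjusted imputation.

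The cost is revised wording and a little more analysis work. No new data are needed, since the IDS is already scheduled at every visit, and the sample size stays at 160.

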#### Randomization

After signing the informed consent form, patients will enroll in the study and start with the baseline interview. After completing the baseline interview, patients will be assigned at random to either the intervention group or the control group. The intervention group will receive CBASP, while the control group will receive treatment as usual. Randomization will be performed by an external researcher using a computerized random number generator. Randomization is stratified per location.

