**Questionnaires for economic evaluation:**					
Registration of usage medication	x				x
TIC-P measures illness and work	x				x
Perceived need for care	x				x
TIC-P work + health care utalization self report			x	x	

**Questionnaires filled in by therapists:**	**Baseline**	**8 week follow-up**	**16 week follow-up**	**32 week follow-up**	**52 week follow-up**

Clinical Global Impression-Improvement (CGI)		x	x	x	x
Working alliance questionnaire, therapist version		x	x	x	

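### The economic analysis names no baseline adjustment although baseline resource use is collected, so the cost comparison may be less precise than the data allow

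*Protocol article*

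**What the plan says.** On the economic side, the Analysis section gives the aim, "The main aim of the economic analysis is to compare the two groups in terms of mean costs and cost-effectiveness", by intention to treat. On method it says "Cost-effectiveness ratios and cost-utility ratios will be calculated using bootstrapping techniques according to the bias corrected percentile method", and then "Bootstrapped cost-effect pairs will be graphically represented on a cost-effectiveness plane". The effect measure is fixed by "The primary outcome measure of the study will be included in the cost-effectiveness ratios". The listed sensitivity analyses vary prices and resource use. No covariate appears anywhere in this paragraph.

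On the clinical side, the same section says "Analysis of covariance, controlling for baseline value will be used to estimate the overall treatment effectiveness (difference in IDS score) at follow-up", and the Abstract adds center as a second covariate.

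On the data, the Economic evaluation section has patients report care use and absenteeism through the PNCQ and the TIC-P, "which patients will fill out four times during the study, at baseline, after 16 weeks, after 32 weeks and at the end of the study". Medication use is also registered from baseline. Table 1 describes the TIC-P row marked at baseline and 52 weeks as "TIC-P measures illness and work x x"; the row that names health care utilisation is marked only at 16 and 32 weeks. On allocation, "Randomization is stratified per location", and no other stratification factor is given.

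**The concern.** Research question 1 asks about effectiveness and cost-effectiveness together. The article names the covariates for the first half and none for the second.

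Prior care use and work absence may well predict later costs. Allocation is balanced only within location, so baseline costs are balanced between arms only by chance, with about 60 evaluable patients per arm. An unadjusted cost difference would carry any such gap into the numerator of the ratio, and its interval would be wider than necessary. The sample size was set on response and no power is stated for costs, so precision that costs almost nothing is worth having. If adjustment is decided only after the cost data have been seen, there will also be two cost differences to choose between.

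**Working it through.** **The plan's own figure.** The Sample size section asks for 60 per condition and 160 in total. With 48% against 73% response (the rates the Background reports for the US trial), two-sided alpha 0.05 and 80% power, the standard formula without continuity correction gives 59 per arm. Power at 60 per arm is 80.8%. Then 120 / (1 − 0.25) = 160. The figure reproduces, but it concerns response and says nothing about precision for costs.

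**Inputs for the check.** n = 60 evaluable per arm (Sample size section). The correlation r between baseline and follow-up cost is not in the documents, so it is assumed over 0.2 to 0.7. Results are in units of the follow-up cost SD, which is not given either.

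**Precision.** The standard error (SE) of an unadjusted mean difference is √(2/60) = 0.183 SD. Linear adjustment for one baseline covariate multiplies it by √(1 − r²), ignoring the small cost of estimating the extra coefficient. The equivalent unadjusted sample is 60 / (1 − r²) per arm.

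| Assumed r | SE factor | Adjusted SE (SD) | SE reduction | Equivalent n per arm |
|---|---|---|---|---|
| 0.2 | 0.980 | 0.179 | 2% | 62.5 |
| 0.3 | 0.954 | 0.174 | 5% | 65.9 |
| 0.5 | 0.866 | 0.158 | 13% | 80.0 |
| 0.7 | 0.714 | 0.130 | 29% | 117.6 |

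**Chance imbalance.** The baseline difference also has SE 0.183 SD. The chance that it exceeds 0.2 SD in either direction is 2(1 − Φ(0.2 / 0.183)) = 0.27. Its 95% limit is 1.96 × 0.183 = 0.36 SD. A baseline gap g shifts the expected unadjusted difference by r × g:

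- gap of one SE (0.183 SD): shift of 0.04, 0.05, 0.09 and 0.13 SD at r = 0.2, 0.3, 0.5 and 0.7;
- gap at the 95% limit, r = 0.5: 0.5 × 0.36 = 0.18 SD, about one SE of the unadjusted difference.

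**Target.** A linear regression coefficient for arm still estimates the difference in mean costs. In simulated trials with 60 per arm, lognormal costs (log SD 1) and no true difference, the adjusted difference averaged within 0.01 of zero. This shows that skewed costs do not rule out the method; it does not estimate the gain in this trial.

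**The case against.** The strongest reply is that the article fixes no unadjusted estimator. A comparison of mean costs is an aim, and a bias-corrected percentile bootstrap works equally well on regression-adjusted differences. Covariates of an economic model are commonly left to a full protocol or analysis plan, which is not shown. This stands: a reader might infer that raw means and unadjusted pairs are planned, but that inference rests on silence.

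A reader might also infer that the trial will report two different IDS effects, an adjusted one as the clinical result and an unadjusted change score on the cost-effectiveness plane, because the primary outcome is worded as a reduction in symptoms. The documents do not support this. The primary outcome enters the ratios, and its stated analysis is an ANCOVA on baseline, so the natural reading is that this same estimate is used.

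Nor would an unadjusted analysis be wrong. Randomisation makes it unbiased, and its interval already allows for chance imbalance. The gain may also be small: patients are newly registered, so earlier use may predict later cost poorly, and the cost of CBASP itself is determined by arm.

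What remains is that the economic paragraph is fairly specific about method and names no covariate, while the paragraph before it does so for the IDS and the baseline data are collected anyway.

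**Conclusion.** The point holds as one of efficiency and chance imbalance, not of bias or invalidity. No baseline adjustment is named for the cost comparison. If none is made, the standard error is larger than it need be by an amount that depends entirely on an unknown correlation: adjustment would remove 2% of it at r = 0.2 and 29% at r = 0.7. With 60 per arm, a baseline gap above 0.2 SD has a 27% chance of occurring. These figures assume equal variances, one linear covariate and 60 evaluable patients per arm. No gain in power for costs can be claimed, because the plan states none. The planned sample size is unaffected.

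**What to change.** State in the economic analysis that, in each bootstrap replicate, patients are resampled within arm and location and two estimates are taken:

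- the cost difference, as the arm coefficient from a linear regression of total cost on arm, baseline cost and location;
- the IDS effect, from the ANCOVA already planned, with baseline IDS and center as in the Abstract.

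Use these two as the cost-effect pair, so that the plane matches the clinical result, and report unadjusted mean costs by arm alongside. Settle this before cost data are compared by arm.

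The cost is some wording and a little code, with no new patients or assessments. Baseline items must be valued with the same unit prices as follow-up items, and missing baseline costs need imputing. Baseline cost should be built from whatever resource items are available at baseline. Table 1 and the Economic evaluation section differ on whether the baseline questionnaire covers care use as well as illness and work, so that should be settled first. A partial baseline cost is still a valid covariate, but may predict less well.
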